### Data sources and collection

As detailed in Table 4, we will use qualitative data from key informant interviews, periodic reflections, clinic surveys, clinic contact logs, and quantitative measures from clinic assessments to address our research aims. In addition to addressing the aims proposed by our ANTECEDENT team, we will also gather the data required to contribute to the cross-site evaluation for all AHRQ EvidenceNOW UAU grantees. Study data is collected and managed using REDCap (Research Electronic Data Capture) tools, a secure, web-based software platform designed to support data capture for research studies [48, 49].

**Table 4 pone.0269635.t004:** Planned data sources, collection strategies, and frequency.

*Data*	*Purpose*	*Source of Data*	*Timing / Frequency* ^a^ ^b^
CCO key informant interviews	To understand how CCOs work with clinics to improve SBIRT and MAUD workflows and documentation, inform baseline understanding or regional context, and to support clinic recruitment.	Interviews with CCO leaders	Within first 12 months of project funding
Clinic contact logs	To monitor clinic engagement, implementation support, changes in context or recipients, adaptations to the intervention, and changes to care delivery.	Practice facilitators complete in REDCap	Following all clinic interactions
Clinic intake Form—Includes SBIRT and MAUD checklist	To describe practice size, staffing, patient population, telehealth utilization, EHR system at time of enrollment. The clinic intake form includes an SBIRT and MAUD checklist used across all grantee programs. This checklist will help determine clinic capacity to capture and report data on intervention outcomes, delivery protocols and inform tailored EHR support.	Survey (online or paper)	Baseline and exit assessment
Needs assessment	To understand clinic interest in and experience with SBIRT, MAUD, and QI, and to inform tailored implementation support.	Pre-intervention meeting with clinics	Baseline assessment
Workflow observation	To understand how clinics deliver SBIRT and MAUD at baseline; to identify promising leverage points.	Observation by practice facilitator	Baseline assessment
HIT capacity assessment	To determine clinic capacity to report SBIRT and MAUD measures; to inform tailored implementation support.	Clinic completes via survey and conversation with practice facilitator	Baseline assessment
Supplemental implementation support plan	To lay out anticipated implementation support plan for each clinic.	Developed by practice facilitator	Within four weeks of clinic baseline assessment
Practice facilitator key informant interviews	To explore how individual facilitators tailor implementation support and the development of personal expertise.	Interviews with practice facilitators	Every six months
Periodic group reflections with practice facilitators	To explore how facilitators tailor implementation support, identify patterns in implementation across clinics, and track adaptations.	Facilitated debriefs with practice facilitators	Monthly
SBIRT and MAUD performance data collection	To identify the proportion of eligible patients receiving SBIRT and MAUD (outcome dependent variable) and ability to report the Oregon CCO metric to their regional Medicaid organization.	EHR or manual tracking	Baseline and exit assessment
Clinic key informant interviews	To understand how clinics experience implementation support and practice facilitator development over time; to understand tailoring of implementation support and facilitator skill development.	Interviews with clinic primary point of contact	Exit assessment

^a^ Baseline assessment activities occur within the first three months of project initiation

^b^ Exit assessment activities occur within the last three months of project support (months 13–15)

CCOs = Coordinated Care Organizations; SBIRT = Screening, brief intervention, and referral to treatment; MAUD = Medication-assisted treatment for alcohol use disorder; HIT = Health information technology; REDCap: Research Electronic Data Capture; EHR = Electronic health record

#### Key informant interviews

We will conduct semi-structured qualitative interviews with three types of key informants: CCO staff, practice facilitators, and clinic primary points of contact. Interviews with CCO staff (N = 15), conducted in the first 12 months of the study, will address how CCOs work with clinics to improve their workflows and documentation for delivery of SBIRT and MAUD, informing a baseline understanding of regional context and supporting clinic recruitment. Every six months, individual semi-structured interviews will be conducted with practice facilitators to gather information about how they tailor implementation support to clinics and develop their expertise. Exit interviews with the clinic primary point of contact will be conducted following implementation. They will provide data about the clinic’s experience with implementation support and the status of their SBIRT performance at the conclusion of the study. All interviews will last 45–60 minutes and will be conducted by qualitative analysts in person or via videoconference. Transcripts will be professionally transcribed and validated for accuracy.

#### Clinic contact logs

Following all clinic interactions, practice facilitators will record field notes in REDCap using structured forms containing open- and closed-ended prompts. Practice facilitators will use two types of structured note-reporting guides to record their interactions and clinic support. Brief communication logs will track short interactions with clinics (e.g., email outreach, scheduling), and in-depth intervention tracker forms will describe engagement, content, and the quality of scheduled facilitation meetings. The logs will produce evaluation data specified in the request for applications, such as the number and type of interactions and implementation strategies employed. The intervention tracker documents practice facilitator tailoring concerning clinic context and perceptions of clinic capacity for change. A qualitative analyst will regularly review the clinic contact logs for completeness.

#### Clinic baseline assessment

The baseline assessment includes five data points: The clinic intake form, needs assessment, workflow observations, HIT capacity assessment, and SBIRT and MAUD performance data collection (Table 4). The clinic intake form is a survey administered to collect details on clinic size, ownership, and electronic health record use. The clinic intake form includes an SBIRT and MAUD implementation checklist. This checklist will help determine a clinic’s capacity to capture and report data on intervention outcomes and inform tailored EHR support. The needs assessment addresses clinic practice culture, external context, and QI capacity. The observation of practice workflows will involve shadowing primary care clinicians and clinic staff to understand clinic culture and workflows related to SBIRT and MAUD. The HIT capacity assessment is used to gauge a clinic’s screening and tracking processes and ability to report the CCO SBIRT metric. In tandem, we will collect SBIRT and MAUD performance data using aggregate quantitative data from clinic EHRs or via manual chart audits. These final two data sources will inform the level of HIT support clinics receive to produce study outcomes data and CCO SBIRT quality metric reporting.

#### Supplemental implementation support plan

Practice facilitators use information from the baseline assessment to develop and refine a tailored supplemental support plan for each clinic in partnership with the clinic’s primary point of contact [50]. This plan draws on findings from the needs assessment. It specifies the anticipated supplemental implementation strategies that the clinic receives (e.g., practice facilitation, HIT support, and expert consultation for SBIRT or MAUD workflows) and whether the activities will occur remotely or in person. The supplemental support plan is delivered over a 9-month implementation period. Supplemental implementation support plans may continue to evolve based on the clinics’ needs and capacity during the active facilitation period; the initial plan and adaptations will be documented in the REDCap database by the practice facilitator.

#### Periodic reflections with practice facilitators

Monthly, a qualitative analyst will facilitate 60-minute periodic reflections with the practice facilitator group via videoconference [51]. The qualitative analyst will solicit discussion topics from study leadership and practice facilitators before each session and develop a short interview guide. The group format will help identify patterns across clinics and facilitators related to clinic context and tailoring of implementation support. Sessions will be recorded, professionally transcribed, and validated for accuracy.

#### Exit assessment

All clinics will participate in an exit consultation, coordinated by the practice facilitator, in the final quarter of the intervention (months 13–15). The closing activities allow solidifying program maintenance and updating the clinic intake form (including the SBIRT and MAUD implementation checklist). During the exit assessment, we will also collect the second set of SBIRT and MAUD performance data to compare SBIRT and MAUD delivery rates to eligible patients at baseline and post-intervention per the specifications of the request for applications and external evaluation. We anticipate that some clinics will develop the capacity for baseline reporting via participation in the intervention. After completing these activities, the practice facilitator will connect the clinic point of contact to the qualitative team to complete the study exit interview. Additional information on the clinic intake form (baseline assessment) and exit interview (key informant interviews) are provided above and in Table 4.

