### Specific aims and study timeline

The aims of ANTECEDENT are to:

Engage, recruit, and conduct needs assessments with 150 primary care clinics and their regional CCOs within the state of Oregon.Implement and evaluate the impact of foundational and supplemental implementation support on SBIRT, MAUD, and quality improvement (QI) capacity in participating primary care clinics.Describe how practice facilitators tailor implementation support based on context, intervention, and personal expertise using mixed-methods and systems science.

Table 1 summarizes the specific aims, research questions, and data sources for ANTECEDENT. Study activities were designed to support engagement and analysis to address the research aims within three years (S1 Table). During grant preparation, we strategically chose not to randomize clinics to different implementation waves or treatment arms and instead allowed clinics to select their preferred quarter to initiate study activities. We anticipate that this approach would optimize a clinic’s ability to engage in support and study evaluation activities. As described by Curran and colleagues, implementation study designs are appropriate after an adequate body of evidence has accumulated that established the efficacy and effectiveness of the intervention [29], as is the case for SBIRT and MAUD [5, 30, 31]. While randomized control trials are often considered the gold standard, they inadequately address “wicked” problems [32] that require attention to individual-, clinic-, and system-level factors and their emergent properties, such as adopting evidence-based practices.

**Table 1 pone.0269635.t001:** Specific aims, research questions, hypotheses, and data sources (N ~ 150 unless specified).

Study Aim	Research Question(s) or Hypothesis	Data Source(s)
1. Engage, recruit, and conduct needs assessments with 150 primary care clinics and their CCOs within the state of Oregon	*RQ 1a*. *How do CCOs work with small to medium sized clinics to achieve OHA’s SBIRT quality incentive metric*?	• Interviews with CCO leaders (N = 15) • Clinic contact logs • Baseline assessment: clinic intake form (including the SBIRT and MAUD implementation checklist), needs assessment, and HIT capacity assessment.
	*RQ 1b*. *How are clinics approaching SBIRT and MAUD and what is their capacity for quality metric reporting*?	

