2. Implement and evaluate the impact of foundational and supplemental implementation support on SBIRT, MAUD, and QI capacity in participating primary care clinics.	*Hyp 2a*: *Clinics with a prior relationship with ORPRN or warm handoff from their CCO will be more likely to engage with and complete all study elements*. *(ADOPTION*, *MAINTENANCE)* *Hyp 3b*: *Practice facilitation to improve QI capacity and increase SBIRT and MAUD will be most effective in clinics with a QI lead*, *clinic champion and routine performance data review*. *(REACH*, *EFFECTIVENESS)*	• Supplemental implementation support plans • Clinic contact logs • Periodic reflections with practice facilitators • Interviews with clinic primary point of contact (N = 150) and practice facilitators • Baseline and exit clinic intake form • Quantitative data on clinics’ SBIRT and MAUD performance
3. Describe how practice facilitators tailor implementation support based on context, intervention characteristics, and personal expertise using mixed-methods and systems science.	*RQ 3a*. *What is the spectrum of tailored implementation support that practice facilitators provide across the participating primary care clinics*?	• Baseline assessment • Clinic contact logs • Supplemental implementation support plans • Periodic reflections with practice facilitators • Interviews with clinic primary point of contact (N = 150) and practice facilitators
	*RQ 3b*. *How do practice facilitators decide to tailor implementation support based on the innovation*, *context*, *and recipients and how does this expertise develop over time*?	

CCOs = Coordinated Care Organizations; SBIRT = Screening, brief intervention, and referral to treatment; OHA = Oregon Health Authority; MAUD = Medication-assisted treatment for alcohol use disorder; ORPRN = Oregon Rural Practice-based Research Network; HIT = Health information technology; QI = Quality improvement

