#### Mixed-methods convergence

Finally, we will merge our quantitative, qualitative, and systems science data using joint displays to reconcile differences and enable the identification of patterns and themes across clinics [57]. To further examine implementation support provided to clinics (Aim 2), we will review descriptive statistics from the clinic contact logs, clinic intake form, and HIT capacity assessment in tandem with our qualitative data. Our goal is to classify clinics along three primary dimensions: (1) baseline capacity, (2) level of implementation support, and (3) observed improvement, and to examine details of the relationships among them. To define baseline capacity, we will categorize clinics as “high”, “medium”, or “low” based on QI infrastructure and workflows for SBIRT and MAUD during the baseline assessment. Qualitative and quantitative analysts will conduct a card sorting activity to classify the participating clinics based on the level of implementation needed to implement SBIRT and MAUD successfully. Analysts will use these resulting categories to create causal predictive matrices to describe clinic features and understand the factors associated with improvement [58]. We will use correspondence analysis to investigate relationships between categorical variables (for example, whether the distribution of implementation support activities varies with clinic baseline capacity) and latent class analysis to identify groups of clinics with similar characteristics. These methods represent high-dimensional data in a low-dimensional space so that it is easier to identify patterns and critical features [59]. We hypothesize that depending on the clinic context, varying levels of implementation support may be needed to support “successful implementation”. We will strive to identify case examples to inform studies using predictive models for tailored implementation support.

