#### Sample size considerations

Recruiting 150 clinics will ensure we retain a minimum of 120 clinics in the final analysis after an anticipated attrition rate of 20% based on prior studies. While we lack preliminary performance estimates for SBIRT for UAU to inform power calculations, for a similar measure—depression screening and follow-up—the OHA reported that CCO performance in the first year of tracking (2014) ranged from 3.3% to 68.1% [60]. Thus, we anticipate similar, significant variability in clinic-level performance outcomes. Our sample of 120–150 clinics ensures that even targeted sub-group analyses performed at the clinic level will have desirable “large” sample properties [59].

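### The clinic interview is scheduled only at exit, so about 120 interviews, not the 150 in Table 1, are expected at the plan's own 20% attrition, and the clinic-side account is selected on completion

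*Protocol article*

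**What the plan says.** Table 1 (Specific aims and study timeline) names the clinic interview as a data source for both Aim 2 and Aim 3: "Interviews with clinic primary point of contact (N = 150) and practice facilitators". The table's heading gives a general figure, "data sources (N ~ 150 unless specified", and the interview entries then state their own N.

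The interview has one time point. Table 4 puts it at the exit assessment. Key informant interviews says: "Exit interviews with the clinic primary point of contact will be conducted following implementation". The Exit assessment section, covering months 13–15, makes it the last step, after the intake form has been updated and the second set of performance data collected: "After completing these activities, the practice facilitator will connect the clinic point of contact to the qualitative team to complete the study exit interview".

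On how many clinics reach that step, the article gives two answers. The Exit assessment section says: "All clinics will participate in an exit consultation, coordinated by the practice facilitator". Sample size considerations expects at least 120 of 150 clinics in the final analysis, "after an anticipated attrition rate of 20% based on prior studies". The Quantitative analytic plan models project completion by logistic regression and defines completion as taking part in the exit assessment. The article describes no interview with clinics that leave early.

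**The concern.** Two things do not fit.

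First, the count. An interview held only at exit cannot be expected from all 150 clinics if a fifth of them are expected to be lost. The claim that all clinics take part in exit has the same problem. It also sits badly with a regression for completion, which presupposes that some clinics do not complete.

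Second, and more important, the selection. According to Table 4, the interview is there to show how clinics experienced the support and how the facilitators developed. If it is offered only at exit, every interviewee comes from a clinic that stayed. For a clinic that left, the sources after baseline are mainly the facilitator's: contact logs, the support plan and its changes, monthly reflections and facilitator interviews. Aim 3 studies how those same facilitators tailor support, so for leavers there is little from the clinic to set beside the facilitator's account. What is at stake is the qualitative evidence in Aims 2 and 3 on why clinics disengage.

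**Working it through.** **Inputs, all from the protocol article**
- Clinics recruited: 150 (Sample size considerations).
- Anticipated attrition: 20% (same section).
- Minimum retained: 120 (same section).
- Clinic interviews listed: N = 150 (Table 1, Aims 2 and 3).
- Timing of the interview: exit assessment only (Table 4, Key informant interviews, Exit assessment).
- Completion: taking part in the exit assessment (Quantitative analytic plan).

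**Step 1: reproduce the plan's own figure.** Retained = recruited x (1 − attrition) = 150 x (1 − 0.20) = 120. This matches the stated minimum. In reverse, 120 / 0.80 = 150, so the recruitment target agrees with the retention target.

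**Step 2: carry it to the interview.** If a clinic lost to attrition has no exit assessment, it has no interview. Expected interviews are then 120 if every retained clinic agrees, and fewer if some decline. The shortfall against Table 1 is 150 − 120 = 30, or 30 / 150 = 20%.

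**Step 3: how far this depends on the attrition rate.**

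| Attrition | Expected exit interviews, 150 x (1 − attrition) |
|---|---|
| 0% | 150 |
| 5% | 142.5 |
| 10% | 135 |
| 15% | 127.5 |
| 20% (the plan's figure) | 120 |

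The listed 150 is met only if no clinic is lost. To obtain 150 interviews with exit-only timing at 20% attrition, the study would have to recruit 150 / 0.80 = 187.5, that is 188 clinics.

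**Step 4: what is available for a clinic that leaves after baseline.**

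| Source | Who provides it | Available for a clinic that leaves? |
|---|---|---|
| Intake form and needs assessment at baseline | Clinic | Yes, but before the support is given |
| Contact logs | Facilitator | Yes, until the clinic leaves |
| Support plan and changes | Facilitator, prepared with the clinic contact | Yes, as recorded by the facilitator |
| Monthly reflections, facilitator interviews | Facilitator | Yes, indirectly |
| Updated intake form | Clinic | No, collected at exit |
| Clinic interview | Clinic contact | No, held at exit |

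Both sources in which the clinic speaks for itself after the support has been delivered are collected at exit.

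**The case against.** The strongest reply is that 150 is the number of clinics to be approached, not a forecast. The table heading uses an approximate N, the sample size section is open about attrition and works with 120–150 clinics, and no qualitative analysis depends on reaching 150 interviews. Part of this stands: the count alone is a labelling matter. But the interview entries state N = 150, and 120 is a fifth lower. The selection remains however the cell is labelled.

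It can also be said that an article leaves withdrawal procedures to the full protocol, which may provide for interviews with leavers. That is possible, and the absence of such a procedure is not in itself the point. The article does fix the timing, the number, the attrition rate and the definition of completion, and these do not agree with one another.

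Several stronger readings are tempting, and the document does not support them:
- *The test of Hypothesis 2a is undermined.* It is not. Completion is the outcome of a logistic regression on prior collaboration, referral route and contacts. Clinics that leave are its non-events and remain in the model.
- *The comparison of successful and unsuccessful clinics is lost.* Completion means reaching the exit assessment, not improving. Completers can include clinics that did not improve and clinics that took only foundational support, so the classification in Mixed-methods convergence keeps its contrast, with fewer clinics at the unsuccessful end.
- *Clinics that cannot supply performance data are barred from the interview.* The Exit assessment section gives an order of events, not a condition. The plan foresees clinics that cannot report and treats that ability as an outcome.
- *Clinics that leave are not heard at all.* They contribute baseline material, may help shape the support plan, and appear in the facilitators' records.
- *The bias can be given a size.* The interviews feed a thematic analysis, and the plan estimates no share of clinics with poorly matched support. Any percentage would rest on invented rates.

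**Conclusion.** The concern holds in a limited form. Table 1's 150 clinic interviews do not fit exit-only timing with 20% attrition: about 120 are expected, 30 fewer. The statement that all clinics take part in exit conflicts with the same attrition figure. The clinic's own account of the support is selected on completion, which weakens the qualitative evidence in Aims 2 and 3 on why clinics disengage. The direction, towards clinics that found the support more workable, is plausible but not shown, and its size is unknown.

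This rests on two assumptions: that clinics lost from the final analysis are those without an exit assessment, which the definition of completion supports but the sample size section does not state; and that all retained clinics agree to the interview. The point concerns the qualitative strand; it does not touch the primary performance outcomes.

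**What to change.** - Offer the clinic interview at withdrawal or at the exit assessment, whichever comes first, with a short version for withdrawing clinics.
- Have the qualitative team contact the clinic directly, so that the invitation does not pass through the facilitator whose support is being discussed.
- State that the interview does not depend on supplying performance data.
- Report themes separately for completing and withdrawing clinics.
- Restate Table 1 as about 120 exit interviews (150 approached) plus withdrawal interviews where the contact agrees, and reword the statement on exit participation to fit the anticipated attrition.

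The cost is small. With 120 exit interviews and at most 30 at withdrawal, the total does not exceed the 150 already planned; only the trigger and the invitation change. The downside is that some withdrawing clinics will decline, so their account will be partial, and the number who decline should be reported.
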